## Abstract

**Background:**

The growth in numbers of older people represents a considerable cost to health and social care services in the United Kingdom. There is an acknowledged need to address issues of social exclusion and both the physical and mental health of this age group. In recent years there has been much interest in the potential contribution of the arts to the health of communities and individuals. There is some evidence that participative singing may be of benefit to older people, however studies to date are limited in number and have lacked rigour. There is therefore a need to build on this knowledge base to provide more quantifiable evidence of both effectiveness and cost effectiveness of singing as a health intervention for this population group.

**Methods:**

The proposed study is a pragmatic randomised controlled trial with two parallel arms. The primary hypothesis is that singing groups for older people improve both physical and mental aspects of quality of life when compared to usual activities. Potential participants will be volunteers over 60 years living in the community and recruited through publicity. Eligible and consenting participants will be randomized to either a singing group or a control group. Singing groups will take part in a twelve week planned programme of singing and control groups will continue with usual activities. The primary outcome measure will be the York SF-12, a health related quality of life measure which will be administered at baseline, three and six months after baseline. The study will evaluate both effectiveness and cost-effectiveness.

**Discussion:**

This study proposes to add to the existing body of evidence on the value of singing for older people by using a rigorous methodological design, which includes a power calculation, a standardised intervention and assessment of cost-effectiveness. It should be regarded as a stage in a progressive programme of studies in this area. If group singing is found to be effective and cost-effective it may offer an alternative means to maintaining the health of people in later life.

**Trial Registration:**

ISRCTN62404401

## Background

The growth of the older population in the UK is substantial and the social care and health needs of older people represent a considerable cost to health and social care services [1]. There is clear scientific evidence of the importance for 'successful aging' of maintaining an active lifestyle-physically, mentally and socially [2] and considerable attention has been given to the need to promote the health of older people, to help them maintain active and independent lives in the community and delay the need for residential care [3]. There is also a need to address mental health problems among the elderly and wider issues associated with social isolation and exclusion.

It is widely understood that the NHS cannot alone address the diverse needs of older people, but has to work in partnership with other statutory bodies and voluntary agencies in the development of services and models of intervention to assist people in living independently and maintaining health and wellbeing [4-7].

In recent years there has been growing interest in the potential value of the arts in addressing significant social issues [8,9]. The social utility of the arts has been promoted by the national Arts Councils, and both DCMS and DH have supported research to explore the contribution of the arts in the field of mental health[10]. The Department of Health established a Review of Arts and Health Working Group which reported in 2007. This led to the Department of Health and Arts Council England publishing A Prospectus for Arts and Health (2007)[11], which provides an overview of the current Arts and Health field in the UK, and offers recommendations for future developments. Coinciding with publication of the Prospectus, Arts Council England published its own strategic framework on Arts, Health and Wellbeing [12].Under the Labour Government the Home Office recognised the value of the arts in work with offenders, and the Treasury funded several projects on arts and community health under the Invest to Save Budget framework (see for example Manchester Metropolitan 'Invest to Save Arts in Health Project' http://www.miriad.mmu.ac.uk/investtosave/.

There is growing recognition of the value of arts activities in improving the lives of older people [13-16], and particularly the value of live music and musical participation for older people [17], including those affected by Alzheimer's and other forms of dementia [18,19]. These studies are useful in highlighting some of the standardized measures which may be employed in studies of arts and health. They do, however, address very disparate interventions within a single study, making cause-effect conclusions problematical. Further, many studies use subjects as their own controls, rather than incorporating a control or comparison group, which would further enhance scientific rigour.

We have recently completed a systematic review of all available non-clinical research studies concerned with the possible benefits of active engagement in singing. A systematic search of the published literature identified 56 reports giving attention to singing and its benefits. Of these reports, 18 were excluded from consideration as being of limited interest. The remaining 36 sources are extremely diverse with respect to the research problem addressed, the participants involved, research design and methods of data gathering and analysis. These papers have been carefully scrutinised but limited synthesis is possible.

Only two studies out of these 36 attempted to assess the wellbeing/health benefits of participation in group singing using standardised measures of health [20,21]. Both studies were concerned with older people. In each study, a positivistic research model was adopted in which pre and post assessments were made of participants in intervention and control groups, with statistical comparison of means between the groups.

Houston et al [20] (UK) assessed the impact of four hour-long sessions of singing over four weeks with 31 residents in three care homes using GHQ-28 and HADS. A non-intervention group of 30 residents in three further care homes were also assessed (mean age 84 years). The authors claim that the intervention group showed significant improvements in measured anxiety and depression over the four weeks compared with the non-intervention group.

Cohen et al. [21] (USA) assessed the impact of weekly participation in a community choir on 90 people aged 65 and older. The study ran over a period of two years, and a range of measures of physical health, health service utilisation, mental health and social activity were employed at pre-test and follow up after one and then two years. A matched non-intervention comparison group (N = 76) were also assessed. The authors claim to find a range of positive effects from participation in the singing group, including higher rating of physical health, fewer doctor visits, fewer falls and better mental health.

Both studies have limitations and both methodological and analytical weaknesses, which raise doubts about the validity of their conclusions. Neither study justified sample sizes in terms of study power. In neither study is there evidence of randomization to intervention or control group, or any formal assessment of cost effectiveness of the intervention.

A central focus of the current proposal is the evaluation of an innovative initiative - the Silver Song Club Project - which provides opportunities for older people to come together on a regular basis to make music and sing, with the support of professional musicians and volunteers drawn from established choral societies and singing groups. Currently, over 40 Silver Song Clubs are in operation across the South East of England, managed by a third sector organization, Sing For Your Life Ltd. (SFYL).

A qualitative and process-oriented formative evaluation has been completed [22], providing information on how the project is run, the experiences of facilitators, volunteers, participants and carers and perceived benefits gained. Data were collected on six of the clubs through observation of sessions, focus groups with volunteers and interviews with club facilitators and participants, venue managers and SFYL directors and facilitators. Older participants have reported positive health benefits across psychological, cognitive, social and physiological domains, supporting previous research findings. There is now a need to develop a more controlled and objective assessment of the benefits for older people of participation in Silver Song Club activities.

### Aims of the study

1. To assess the effectiveness for older people of active engagement in community music activities on measures of physical and mental health.

2. To evaluate the cost-effectiveness for older people of active engagement in community singing.

## Methods

The study is a pragmatic randomised controlled trial with two parallel arms. The study has been granted ethical approval by Surrey Research Ethics Committee REC ref: 10/H1109/5 and complies with the Helsinki Declaration.

### Hypotheses

#### Primary hypothesis

Stated as null hypothesis

Singing groups for older people are no better than usual activities in increasing health-related quality of life in older people measured six months after randomisation using the York SF-12.

#### Secondary hypotheses

Stated as null hypotheses

1. Singing groups for older people are no more cost-effective than usual activities

2. Singing groups for older people are no better at reducing anxiety and depression when compared with usual activities at six months after randomisation measured using the Hospital Anxiety and Depression Scale (HADS).

### Participants

#### Inclusion criteria

The study will, as far as possible, reflect the inclusive nature of existing Silver Song Clubs. Participants will be adults over 60 years of age, able to speak English and able both to provide informed consent and to complete questionnaires.

#### Exclusion criteria

Individuals unable to provide informed consent or complete questionnaires in English.

#### Recruitment

Researchers, in conjunction with the third sector partner organization providing the intervention, will seek suitable venues across East Kent for song clubs to take place. Adverts will be placed in the venues and local newspapers and leaflets will be delivered to homes within the vicinity of the venues. These will specify the locality of the five venues and request that interested individuals should specify a locality to which they will be attached should they decide to take part. Adverts will also state that participants will be randomly allocated into either the singing group or the 'usual activities' group within that area. Local radio publicity will also be sought. Two 'taster sessions' will be held in each venue which will include the provision of information, an invitation for questions and an opportunity for individuals to sample the nature of the proposed intervention programme. A dedicated phone line and email address will be set up to deal with responses and queries and a proforma will be devised to collate details of those volunteering to participate. Personal details will be held in a locked filing cabinet within the research centre.

#### Randomisation and consent

All individuals indicating an interest in taking part will be sent a baseline questionnaire. They will also be sent an information sheet outlining the purpose of the study and what to expect if taking part, plus a consent form to be returned with the questionnaire.

All returned, consented questionnaires will be randomly assigned to either intervention or control arm within one of five geographical areas. Randomisation will be conducted using the secure remote randomisation service based at the University of Kent. Because of the known preponderance of women in singing groups, stratification by gender will be used. Individuals who would attend together if allocated to a singing group (e.g. couples or friends providing transport) will be randomised in pairs on request.

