### Sample size

A power calculation was carried out for the primary outcome (health related quality of life measured on the York version of the SF-12). There are no previous randomised controlled trials evaluating the impact of singing groups on quality of life in this population. Using data from quasi-experimental and observational studies we hypothesise that a minimally important difference in health related quality of life between the intervention group and control groups is in the order of 5 points on the York SF-12, equivalent to a medium effect size difference of 0.5. To detect this difference using a two-tailed test, alpha of 0.05 and power at 80% requires 63 participants in each of the two arms, a total of 126. We anticipate 5 singing groups and 5 controls and need to take account of any clustering effect in calculating sample size. We have used a conservative estimate of intra-class correlation coefficient of 0.02, similar to general practice populations and a cluster size of 12. This inflates the required sample size by a factor of 1.2, 77 in each group, a total of 154. Previous research would suggest the loss to follow up at 6 months for this population would be in the order of 20% and this further inflates the sample size to 92 in each group, a total of 184. We do not anticipate that all those enquiring would be willing to take part in the evaluation but we do have evidence that the consent rate would be in the order of 70%. This would mean we would require a total of 240 potential participants, 24 in each singing group and control group over the course of the study.

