### Data analysis

#### Effectiveness analysis

Data analysis will be conducted blind to the allocation of participants. The primary analysis will be intention to treat, where participants are analysed as part of their randomised group irrespective of their attendance. This provides the most pragmatic estimate of effectiveness. The primary outcome measure, the SF-12, will be analysed at 6 months using analysis of covariance to adjust for baseline differences between the groups. Due to the clustered nature of the study in which participants are nested within singing groups multi-level modelling will be undertaken to adjust for any cluster effects. Results will be presented as means and 95% confidence intervals. Secondary outcomes will be analysed in a similar manner. We will also explore the potential efficacy of the intervention by conducting a per protocol analysis in which only those participants who attended at least 50% of sessions are included. Other secondary analysis will include a regression analysis to explore both potential predictors of outcome and any baseline x treatment interactions.

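### Some participants are randomised in pairs, but the sample size and the multi-level model cluster by singing group only, so the extra within-pair correlation is not accounted for

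*Protocol article*

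**What the plan says.** Three sections of the protocol article bear on this.

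- **Randomisation and consent.** Consenting respondents are "randomly assigned to either intervention or control arm within one of five geographical areas". Because women are expected to predominate, "stratification by gender will be used". The next sentence makes an exception for people who would attend together: "e.g. couples or friends providing transport) will be randomised in pairs on request". Neither the expected number of pairs nor the stratum for a pair of one man and one woman is given.
- **Sample size.** The authors anticipate five singing groups and five controls and say that they "need to take account of any clustering effect in calculating sample size". They use an intra-class correlation of 0.02 and a cluster size of 12. Pairs are not mentioned.
- **Effectiveness analysis.** The 6-month SF-12 is analysed by analysis of covariance with baseline adjustment. The clustering is described in these words: "participants are nested within singing groups multi-level modelling will be undertaken to adjust for any cluster effects". Secondary outcomes are handled in a similar manner. Pairs are again not mentioned.

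**The concern.** Two people randomised together always share an arm, so together they give one allocation, not two. Partners, and to a lesser degree friends, can be expected to have correlated quality of life and mood. These are what the SF-12 (primary outcome) and the HADS (secondary outcome) measure. That correlation exists in both arms, because pairs are formed before allocation.

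The only level named in the model is the singing group. Within a group, one common correlation of 0.02 cannot represent two people who share a household. Control participants carry on with their usual activities and attend no trial group, so nothing in the stated nesting describes a control-arm pair. If part of the randomisation structure is left out of the model, standard errors tend to be too small, confidence intervals too narrow, and the test somewhat above its nominal 5%. If it is put into the model without an allowance in the sample size, some power is lost.

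**Working it through.** **Inputs from the Sample size section.** The difference is "5 points on the York SF-12, equivalent to a medium effect size difference of 0.5", which implies an SD of 10. The test is specified as "using a two-tailed test, alpha of 0.05 and power at 80" per cent. The result before clustering is "requires 63 participants in each of the two arms, a total of 126". The intra-class correlation is 0.02 and the cluster size 12.

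**Inputs that are assumed.** The article gives neither p (share of participants in pairs) nor rho (within-pair correlation of the outcome that remains after baseline adjustment). Both are taken as 0.2 to 0.4, with a smaller case for comparison.

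**Step 1: reproduce the plan's figures.**
- n per arm = 2(1.96 + 0.8416)² / 0.5² = 62.8, rounded up to 63.
- Design effect = 1 + (12 − 1) × 0.02 = 1.22.
- 63 × 1.22 = 76.86, rounded up to 77 per arm, 154 in total.

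The stated 77 is thus fully explained by the group-level factor. Nothing in it is for pairs.

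**Step 2: add the pair level.** A paired member of a group of 12 has 11 fellow members. One of them is the partner, whose correlation is rho instead of 0.02. For that person the design effect is 1.22 + (rho − 0.02). Averaged over all participants:

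design effect = 1.22 + p(rho − 0.02)

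**Step 3: consequences.**
- Type I error if pairs are ignored = 2[1 − Φ(1.96 / √(design effect / 1.22))], a large-sample approximation.
- Power if pairs are modelled, with 77 evaluable per arm = Φ(0.5 × √(77 / (2 × design effect)) − 1.96).
- Evaluable n per arm needed = 63 × design effect, rounded up.

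| p | rho | Design effect | Type I error, pairs ignored | Power at 77 per arm, pairs modelled | n per arm needed |
|---|---|---|---|---|---|
| 0 | – | 1.220 | 5.0% | 80.2% | 77 |
| 0.1 | 0.1 | 1.228 | 5.1% | 79.9% | 78 |
| 0.2 | 0.2 | 1.256 | 5.3% | 79.1% | 80 |
| 0.3 | 0.3 | 1.304 | 5.8% | 77.5% | 83 |
| 0.4 | 0.4 | 1.372 | 6.5% | 75.4% | 87 |

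Worked example for the last row: 1.22 + 0.4 × 0.38 = 1.372; 1.372 / 1.22 = 1.125; 1.96 / √1.125 = 1.848, a two-sided tail of 6.5%. For power, 77 / 1.372 = 56.1 and 0.5 × √(56.1 / 2) − 1.96 = 0.69, which gives 75.4%.

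**The case against.** Several objections have force.

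- **The plan does not treat participants as independent.** A reader might infer from the silence on pairs that it does. The documents do not support that: the sample size carries a factor of 1.22 and the analysis is multi-level, so two partners in one group already share a correlation of 0.02. Only the excess over that is missing. For the same reason it would be wrong to apply a pair factor of 1 + p × rho to the unclustered 63; the base is 77 with 1.22.
- **The sample size may hold some slack.** The factor 1.22 is applied to both arms, although controls do not meet. If clustering among controls is in fact negligible (an assumption), the control arm needs only 1 + p × rho, and the average over arms is 1.11 + p × rho − 0.01p. That is 1.15 at p = rho = 0.2 and 1.20 at 0.3, both under 1.22, and 1.27 at 0.4 (power 78.7% at 77 per arm). This stands as a point about power. It does not repair standard errors computed without a pair level.
- **Baseline adjustment removes part of the correlation.** Shared and stable influences are partly absorbed by the baseline score. This stands, and is why rho is defined here as a residual correlation. The upper end of its assumed range may be high.
- **Pairing is only on request.** If few people ask for it, the effect nearly vanishes: at p = rho = 0.1 one more participant per arm is needed.
- **An analysis plan or full protocol may deal with pairs.** Identifiers and model levels are often left to such documents, and a pair level would not contradict the promise to adjust for cluster effects. But the article itself states the allocation rule, the clustering allowance and the nesting. The last two do not match the first.
- **Mixed-sex pairs.** A reader might infer that such a pair cannot be stratified at all, or that the two randomisation rules exclude each other. That is too strong. Same-sex pairs fit the gender strata, and a mixed pair can have its own stratum or be stratified by area alone. The rule is unstated, not impossible, and a condensed article may leave it to the randomisation specification.

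**Conclusion.** The point holds in a limited form. For some participants the pair is the unit of randomisation, and neither the sample size nor the stated model has a pair level; for control-arm pairs the model as described has no clustering term at all.

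Under the assumed p and rho of 0.2 to 0.4, the design effect is 1.26–1.37 instead of 1.22. Type I error is about 5.3–6.5% if pairs are ignored, and power at 77 evaluable per arm is about 79–75% if they are modelled. These figures rest wholly on the assumed values and on a large-sample approximation. With few pairs they shrink to almost nothing. The omission is certain from the text; its size is not, and it should not be presented as a proven inflation of the error rate. The unstated stratum for mixed-sex pairs is a request for clarification and no more.

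**What to change.** 1. Record a pair identifier at randomisation, with singletons as units of size one. This is the time-critical part, since pairs that are not recorded then may not be recoverable later.
2. In the Effectiveness analysis section, include the randomisation unit as a random effect, or as the level of a cluster-robust variance, in both arms and for primary and secondary outcomes, alongside the group level already planned.
3. In the Sample size section, state an assumed p and rho and restate the design effect, for example as 1.22 + p(rho − 0.02), or the power that results at the planned n.
4. For clarification, state how a mixed-sex pair enters stratification, for example through a separate pair stratum or by stratifying pairs by area only.

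The cost is one extra data field, one model term and slightly wider intervals. If pairs turn out to be rare, almost nothing is lost.

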### Intervention

The Silver Song Club model is a well established format for participative singing for older people and this will be replicated in a standardised form. Trained and experienced facilitators under the guidance of SFYL will meet to compile a twelve week 90 minute programme comprising songs from different eras and a variety of genres. This will be followed by a series of 'unification' meetings, to ensure that all facilitators are aware of how to access the material and deliver it in the same way (e.g. accompaniment, key, acquiring copyright etc). The programme will be developmental, progressing from singing melody lines to harmonising, layering and singing in rounds. Chime bars will also be introduced where appropriate and there will be an opportunity for participants to request items. All clubs will deliver the same programme concurrently, and consistency will be monitored by a programme manager who will make unannounced visits to each club 5-6 times during the intervention. A song book will be especially produced for the trial and a register of attendees will be maintained.

